#### **Nature and extent of the burden and risks associated with participation, benefit and group relatedness:**

At baseline, when a meniscal tear is suspected at presentation, an MRI-scan will be obtained. This is not seen as an extra burden for participants, since an MRI which has a high sensitivity and specificity normally is usually made to avoid unnecessary diagnostic arthroscopies as stated in the guideline for arthroscopy of the knee, 2010 (NOV) (1).

All patients approached and willing to participate in the trial will be randomized when all inclusion criteria are met when they return to the outpatient department for the results of the MRI.

Participants will be randomized into the surgical group or the conservative group and are followed at 3, 6, 9, 12, 18 and 24 months.

The risks associated with participation in the trial include the general risks for surgery, e.g. infection, bleeding, postoperative numbness, paralysis, pain, persistence of symptoms when randomized into the surgical group. In the conservative group, no specific risks are known to occur. Since surgery is current standard treatment, there are no additional risks for participation in this trial.

All patients will return to the outpatient department after 3 and 24 months. This will be for PE (3 months) and X-rays (24 months).

We plan a follow up moment at 60 months to see the progression of osteoarthritis, measured with the Kellgren Lawrence Grading Scale for Osteoarthritis.

The burden of the extra X-ray will be negligible, especially when focused on the potential outcome of the trial, which could lead to a significant reduction of unnecessary surgeries.

All questionnaires will be obtained digitally and can be completed at home. If preferred, a hardcopy can be sent to these participants.

Completion of the questionnaires will take approximately 30 minutes. The questionnaires at 9 and 18 months consist only of the EQ-5D-5L and TiC-P and will take only 5 minutes to complete.

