## 8. METHODS

### 8.1 Primary and secondary outcome measures

#### 8.1.1 Primary outcome

Primary outcome will be change in physical function from baseline to 2 years measured by the International Knee Documentation Committee (IKDC) 'Subjective Knee Form', which has been validated for meniscal injuries (18). The IKDC is developed for knee-specific measurement of symptoms, function, and sports activities in patients with ligament and meniscal injuries. The IKDC is a self-administered questionnaire with a total of 19 questions. All items, except item 10a, are converted to a score with a maximum of 100 indicating no restrictions in daily and sports activities and the absence of symptoms. A difference of more than 8.8 points in IKDC-score is deemed clinically relevant.

In addition, we will perform an economic analysis alongside the RCT from a societal perspective and a budget impact analysis from societal, government and insurer perspective.

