#### 8.4 Study scheme

At the initial presentation, an MRI-scan will be obtained when a meniscal injury is suspected. Patient will also be informed about the trial and will be given a patient information latter. In case a meniscal injury is diagnosed, patients will be asked to participate in the trial.

After informed consent is signed at the outpatient department (t0), patients will be entered in an online randomization program and are assigned to either arthroscopic partial meniscectomy (within 4 weeks) or physical therapy. They are asked to complete CRF t0. 3 months after treatment, they will return to the outpatient department to check for function. A physical examination is performed, and they will be asked to complete CRF t2. At both 6 (t3), and 12 (t4) months they will not visit the outpatient department and they are online asked to complete the corresponding CRF. For an overview of assessments, see figure 1 or table 1. At 24 months they will be asked to visit the outpatient department for an X-ray and to complete CRF t5 as endpoint of the study.

In case patients in the physical therapy group don't show any improvement, they will be held the choice of delayed arthroscopic partial meniscectomy. This will be determined by agreement between participant and surgeon. Each CRF is calculated to take no more than 30 minutes.

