**Table 1: measurement moments**

| Baseline (t0) | 1-2 months
(t1) | 3 months
(t2) | 6 months
(t3) | 9 months
(t4) | 12 months
(t5) | 18 months
(t6) | 24 months
(t7) |
|---------------|--------------------|------------------|------------------|------------------|-------------------|-------------------|-------------------|
| CRF-1  |                    | CRF-2     | CRF-3     | CRF-4     | CRF-5      | CRF-6      | CRF-6      |
| Visit 1       | Treatment          | Visit 2          | No visit         | No visit         | No visit          | No visit          | visit 3           |
| Randomization | APM or PT          |                  |                  |                  |                   |                   |                   |
| IKDC          |                    | IKDC             | IKDC             |                  | IKDC              |                   | IKDC              |
| RAND-36       |                    | RAND-36          | RAND-36          |                  | RAND-36           |                   | RAND-36           |
| EQ-5F5L       |                    | EQ-5D5L          | EQ-5D5L          | EQ-5D5L          | EQ-5D5L           | EQ-5D5L           | EQ-5D5L           |
| VAS           |                    | VAS              | VAS              |                  | VAS               |                   | VAS               |
| TAS           |                    | TAS              | TAS              |                  | TAS               |                   | TAS               |
| PSC           |                    | PSC              | PSC              |                  | PSC               |                   | PSC               |
| TiC-P         |                    | TiC-P            | TiC-P            | TiC-P            | TiC-P             | TiC-P             | TiC-P             |
| PSC           |                    | PSC              | PSC              |                  | PSC               |                   | PSC               |
| PE            |                    | PE               |                  |                  |                   |                   |                   |
| X-ray         |                    |                  |                  |                  |                   |                   | X-ray             |

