## 10. STATISTICAL ANALYSIS

Data-analysis and presentation:

To investigate the effect of surgery, we will use generalized estimating equations (GEE) for longitudinal analysis in SPSS 18 on an intention-to-treat and per-protocol basis, as well as sub-group analysis of the cross-over patients. This method takes into account the dependency of observations within a patient, and the fact that not all patients may be assessed at each time point (missing data). In the primary GEE model, the outcome variable studied (e.g. physical function on the IKDC) will be analyzed as a dependent variable, using treatment allocation (1, intervention; 0, control) and time as a key independent variables. In the secondary GEE model, the outcome variables studied (e.g. general health on the RAND36, quality of life on the EQ5D-5L, level of activity on the TAS, knee pain on the question 10 of IKDC, the correlation between a patient's expectation and satisfaction, productivity losses on TiC-P, muscle strength, range of motion, squatting and adverse events) will be analyzed in a similar way. To evaluate whether the two groups differed in change over time the interaction term of group and time (group X time) will be assessed. Time will be included as a dummy variable (reference = baseline T0), and four interaction terms will be analyzed (T1Xgroup; T2x group; T3x group, T4x group). All models will be corrected for center of inclusion and age group. In additional analysis, we will investigate the possible confounding effect (defined as more than 10% change in the parameter estimate for groupXtime) of 5 variables (body mass index, gender, profession, ASA-classification, the affected meniscus, the type of tear and the stadium of OA according to the Kellgren Lawrence Grading Scale for Osteoarthritis).

At the following time points following the treatment (T2, T3, T5 and T7) we will describe the incidence of revisions (intervention group) or treatment failures (=delayed APM, control group) using descriptives. After two years (T7) we will compare the incidence of development or progression of OA between groups using a chi-squared test (or Fisher's Exact as appropriate). For all analysis, a two-tailed value of  $p < 0.05$  is considered to be significant.

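### The group-by-time terms listed in Section 10 (T1 to T4) do not match the IKDC visits (T2, T3, T5, T7), so as written the primary model has no term for the 24-month endpoint

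*Protocol*

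**What the plan says.** Section 8.1.1 defines the endpoint: "Primary outcome will be change in physical function from baseline to 2 years", measured by the IKDC Subjective Knee Form. The follow-up part of Section 5 also places the primary endpoint at two years.

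Section 10 gives the model. On time coding it says "Time will be included as a dummy variable (reference = baseline T0"). On the comparison of interest it says "To evaluate whether the two groups differed in change over time the interaction term of group and time (group X time) will be assessed". It then lists the terms: "four interaction terms will be analyzed (T1Xgroup; T2x group; T3x group, T4x group"). Secondary outcomes are to be handled in a similar way.

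The visit labels appear in three places:

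- Table 1 runs from t0 to t7, and its later columns read "9 months (t4) | 12 months (t5) | 18 months (t6) | 24 months (t7").
- The Section 8.4 text (Study scheme) numbers differently: "At both 6 (t3), and 12 (t4) months they will not visit the outpatient department". It gives the 24-month form the label t5.
- The next paragraph of Section 10 follows Table 1 when it describes revisions and treatment failures: "At the following time points following the treatment (T2, T3, T5 and T7"). It then uses T7 for two years.

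The burden paragraph in Section 6.3 confirms which visits lack the IKDC: "The questionnaires at 9 and 18 months consist only of the EQ-5D-5L and TiC-P".

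**The concern.** With time entered as dummies and baseline as reference, the coefficient of a visit dummy times group is the between-group difference in change from baseline to that visit. The primary estimate of this non-inferiority trial is therefore the 24-month-by-group coefficient, which is the quantity to compare with the 8-point margin in Section 6.4. If the written list of interactions leaves that coefficient out, the sentence that fixes the primary model does not deliver the primary estimate.

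Three features of the plan raise the stakes:

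- The trial is open-label, and Section 5 plans a first evaluation at one year. An unclear primary contrast leaves room to settle the time point after results are visible.
- The confounder rule in Section 10 refers to a change of more than 10% in one group-by-time estimate. With four such estimates, the rule cannot be applied until one is named.
- The same sentence carries over to secondary outcomes, some of which have a different number of visits.

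**Working it through.** No arithmetic is needed; the check maps the listed terms onto the visit schedule.

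**Step 1. Where the IKDC is measured (Table 1).** It is scheduled at t0, t2, t3, t5 and t7, which gives four post-baseline visits at 3, 6, 12 and 24 months. The t1 column (1-2 months) is the treatment period and has no questionnaire. The t4 and t6 columns (9 and 18 months) have only EQ-5D-5L and TiC-P, as the burden paragraph confirms.

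**Step 2. The listed terms under each printed numbering.**

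| Listed term | Table 1 | IKDC at that Table 1 visit? | Section 8.4 text |
|---|---|---|---|
| T1 | 1-2 months | no | not defined |
| T2 | 3 months | yes | 3 months |
| T3 | 6 months | yes | 6 months |
| T4 | 9 months | no | 12 months |
| Label of 24 months | t7 | yes | t5 |

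Under Table 1, two of the four terms (T1, T4) have no IKDC data, and the IKDC visits T5 and T7 have no term. Under the Section 8.4 text, T2 to T4 reach 12 months and 24 months (t5) is again outside the list.

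**Step 3. Numberings that are not printed.** Counting all the follow-ups named in Section 5 in order (3, 6, 9, 12, 18, 24 months) would make T1 to T4 the 3-, 6-, 9- and 12-month visits, and 24 months would be T6. Counting only the IKDC follow-ups in order (3, 6, 12, 24 months) would make T4 the 24-month visit. That is the only index that fits the list. It is stated nowhere and conflicts with the use of T7 for two years in the next paragraph of Section 10.

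**Step 4. What the literal model would do.** Write the mean as b0 + b1·G + sum of c_k·T_k + sum of d_k·T_k·G, where G is group. The wanted quantity is d at 24 months. Suppose all IKDC visits keep their time dummies but only T2 and T3 have usable interactions. The group difference is then forced to be the same (b1) at baseline, 12 months and 24 months. The difference in change from baseline to 24 months is fixed at zero and is not estimated. The T2 and T3 interactions would also no longer be differences in change from baseline, because b1 pools three visits.

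**Step 5. Other outcomes.** RAND-36, VAS, Tegner and PSC share the IKDC schedule. EQ-5D-5L and TiC-P have six follow-ups (t2 to t7). Physical examination has one (t2). Four terms fit neither of the last two schedules.

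**The case against.** The strongest reply is that this is a slip in numbering. Section 10 asks for exactly four terms with baseline as reference, and the IKDC has exactly four follow-ups. Read as a consecutive count, the list fits one to one. The endpoint is fixed at two years in Sections 5 and 8.1.1, Section 6.4 allows for loss to follow-up at 24 months, and Section 10 promises that a statistician will be consulted on all GEE analyses. Terms for T1 and T4 could not be fitted to IKDC data, so the error would show at the first run. Formal naming of the primary contrast is also often left to a statistical analysis plan, which is not at hand.

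Most of this stands. It explains the likely cause and makes harm less probable. It does not make the sentence right: the protocol states a specific list, and its own tables contradict it for the coefficient that matters most.

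Three stronger readings are tempting and are not supported:

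- A reader might infer that the 24-month visit was meant to be dropped from the analysis. The two-year endpoint and the count of four argue against that.
- A reader might infer that an analyst would test non-inferiority at 3 or 6 months. The endpoint sections name two years, so this does not follow.
- A reader might take the first description of the primary model, with only treatment and time, as a main-effects model that averages over visits and dilutes a late difference. The same paragraph then assigns the comparison of change over time to the group-by-time interaction, so that reading is not required.

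**Conclusion.** The inconsistency is real and sits in the primary-model specification. Under both visit numberings printed in the protocol, T1 to T4 excludes 24 months, so the model as written has no interaction term for the primary endpoint. By Table 1, two listed terms are without IKDC data and two of the four IKDC follow-ups are without a term.

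The probable cause is leftover consecutive numbering, and the intended model is probably the right one. That is an inference from the matching count of four; the text does not say it. The conclusion rests only on the labels in Table 1, the Section 8.4 text and Section 10. It makes no numerical claim about bias or power. The sample size of 160 per group is unaffected, since it is derived from the power, alpha, standard deviation, margin, loss to follow-up and delayed-surgery rate, and does not depend on the interaction list.

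**What to change.** In Section 10:

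- For the IKDC and outcomes on the same schedule, replace the list with T2, T3, T5 and T7 by group.
- State that T7 by group (24 months) is the primary estimate, to be compared with the non-inferiority margin.
- For other outcomes, tie the terms to their own visits in Table 1: six follow-ups (T2 to T7) for EQ-5D-5L and TiC-P, and T2 only for physical examination.

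Use a single visit numbering in the Section 8.4 text, Table 1 and Section 10. Table 1 is the natural choice, because Section 10 already uses it for the revision and osteoarthritis analyses.

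The cost is a sentence or two and some label corrections. No visit, questionnaire, patient number or procedure changes, and there is no statistical downside.

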#### **4. OBJECTIVES**

The objective of this study is to evaluate the effectiveness and cost-effectiveness of surgical and conservative treatment of non-obstructive meniscal injuries in older patients

Hypothesis:

We assume equal improvement of physical function in both groups and reduced costs with conservative treatment.

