#### 6.4 Sample size calculation

Sample size is based on a power of 90%, an alpha of 0.05, a standard deviation of 18 points and a non-inferiority threshold of 8 points on the IKDC (a minimal clinical important change in IKDC is 8.8) (18).

We calculated that with 10% loss to follow-up after 24 months and 25% delayed APM in the PT group, 160 patients are needed per group in this non-inferiority RCT.

This corresponds to a total of 320 patients will be included.

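### The 10% change rule for confounders is relative to a group-by-time estimate that the trial expects to be near zero, so it does not measure confounding; the covariate set of the supportive analysis is left to chance

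*Protocol*

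**What the plan says.** Protocol section 10 sets out a GEE model with treatment, time and their interaction. Time is a dummy variable with baseline as reference, and "four interaction terms will be analyzed (T1Xgroup; T2x group; T3x group, T4x group"). Adjustment of every model is fixed: "All models will be corrected for center of inclusion and age group". A further step follows: "In additional analysis, we will investigate the possible confounding effect". The criterion and the count are given as "possible confounding effect (defined as more than 10% change in the parameter estimate for groupXtime) of 5 variables", and the list reads "body mass index, gender, profession, ASA-classification, the affected meniscus, the type of tear and the stadium of OA" by Kellgren-Lawrence grade. That is seven variables.

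The expected treatment effect is in section 4: "We assume equal improvement of physical function in both groups". Section 8.1.2 repeats it, with equality taken as a difference below 8.8 IKDC points. Section 6.4 bases the sample size on "a power of 90%, an alpha of 0.05, a standard deviation of 18 points and a non-inferiority threshold of 8 points".

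The protocol does not say:
- which of the four interaction terms the 10% refers to;
- whether a candidate covariate enters as a main effect or together with its interaction with time;
- what is done with a variable once it is flagged.

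**The concern.** A relative-change criterion needs a denominator that is reliably away from zero. Here the denominator is the group-by-time estimate, which the trial hopes and expects will be close to zero. A variable can then be called a confounder because the treatment estimate happens to be small, not because the variable distorts it. If the estimate is 1 point, a shift of 0.1 point is enough, which is about 1% of the 8-point margin.

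The candidates are baseline characteristics in a trial randomized 1:1 and stratified by center and age group. The intention-to-treat comparison therefore has no systematic baseline confounding to detect, and any imbalance is chance. What is at stake is the supportive adjusted analysis. Its covariates would be picked by a rule that does not do what its name says, from a list whose length the text states inconsistently.

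**Working it through.** **The plan's own figure.** The protocol gives no number for the 10% rule, but its sample size can be reproduced, which confirms the inputs. Section 10 tests two-tailed at 0.05 ("For all analysis, a two-tailed value of" p < 0.05), so non-inferiority is one-sided at 0.025. Per arm:

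n = 2 × 18² × (1.96 + 1.2816)² / 8² = 106.4, rounded up to 107.

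Dividing by (1 − 0.10) × (1 − 0.25) for loss to follow-up and delayed surgery gives 107 / 0.675 = 158.5, so 159. The plan states 160.

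**Scale of the trigger.** After 10% loss, 160 per arm becomes 144. Taking the SD of 18 as the SD of change:

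SE = 18 × √(2/144) = 2.12 points; 95% CI half-width = 1.96 × 2.12 = 4.16 points.

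If the true difference is 0, an estimate of one SE is typical. The trigger is then 0.1 × 2.12 = 0.21 points, or 2.7% of the 8-point margin.

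**Reading 1: covariate enters with time (equivalent to adjusting the change score).** Let r be the correlation between covariate and change. This is an assumption, since the documents give none. Chance imbalance moves the estimate by r × SE × U, and the crude estimate is SE × (rU + √(1 − r²) V), where U and V are independent standard normals and the true difference is 0. The rule fires when |rU| > 0.1 × |rU + √(1 − r²) V|. Since V/U is Cauchy, with s = √(1 − r²):

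P(flag) = [arctan(9r/s) + arctan(11r/s)] / π.

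| r | arctan(9r/s) | arctan(11r/s) | P(flag) |
|---|---|---|---|
| 0.05 | 0.423 | 0.503 | 0.30 |
| 0.1 | 0.735 | 0.836 | 0.50 |
| 0.2 | 1.072 | 1.152 | 0.71 |
| √0.05 = 0.224 (5% of variance) | 1.120 | 1.194 | 0.74 |
| 0.3 | 1.231 | 1.289 | 0.80 |

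The SE cancels, so at a true difference of 0 a larger trial would not cure this for a given r.

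The formula takes the covariate's coefficient as known. Simulating whole trials with it estimated (144 per arm, SD 18, least squares on change with and without each covariate) gave, over repeated runs:

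- true difference 0, unrelated covariate: flagged in 24% to 26%;
- true difference 0, covariate explaining 5% of variance: 70% to 73%;
- true difference 0, seven unrelated covariates: at least one flagged in 65%;
- true difference 8, unrelated covariate: 0.2% to 0.3%.

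The same covariate is thus flagged or not mainly according to how close the treatment estimate lies to zero.

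**Reading 2: covariate enters as a main effect only.** A baseline variable shifts all of a patient's visits by the same amount. With complete data this cancels from the change since baseline, so group-by-time does not move. In simulated exchangeable GEE fits (160 per arm, five IKDC visits) the rule fired in 0% of trials. With 10% to 25% random dropout and a true difference of 0 it fired in about 10% to 40%, for median shifts of only 0.03 to 0.11 points.

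**Size of the effect on the estimate.** Under reading 1 with a true difference of 0, adjusting for every flagged covariate out of seven moved the estimate as follows (144 per arm):

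| Correlation of each covariate with change | Median shift | 95th percentile |
|---|---|---|
| unrelated | 0.1 | 0.6 |
| r = 0.1 | 0.3 to 0.4 | 1.0 to 1.2 |
| r = 0.2 | 0.7 | 2.1 to 2.2 |

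At 108 per arm and r = 0.2, the 95th percentile was 2.4.

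**The case against.** The strongest reply is that nothing decisive hangs on the rule. It sits in an additional analysis, every model is already fixed on center and age group, and no sentence carries a flagged variable into the primary model or the non-inferiority decision. A reader might infer that the trial's conclusion, or the adjusted estimate itself, becomes arbitrary. The documents do not support that. Only the covariate set is arbitrary, and the estimate usually moves little compared with the margin and the CI half-width of about 4 points. This part of the reply stands, and it limits the point.

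Other replies stand in part:
- Section 10 also plans per-protocol and cross-over analyses, and anticipates 25% intervention-related dropout. Randomization does not protect those comparisons, so looking at confounding there is legitimate. It does not rescue a relative threshold around zero.
- A named list with a numeric cut-off leaves less discretion than an open search. The end of the Budget Impact Analysis section also says analysts are blinded by coded treatment. Blinding limits deliberate choice, but not selection by chance.
- The form of covariate entry might be settled in a statistical analysis plan not at hand. That would decide between the two readings, but neither gives a working measure of confounding.
- The chance behaviour depends on a true difference near 0 and largely disappears for weak covariates near 8 points. This is correct, but near 0 is what the protocol assumes.

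**Conclusion.** The rule as written does not measure confounding. If covariates enter with time and the true difference is near 0, it fires largely by chance: about 25% for an unrelated covariate, about 70% for one explaining 5% of variance, and about 65% for at least one of seven unrelated ones. If they enter as main effects with complete data, it cannot fire. The count of five contradicts the seven variables listed, and the interaction term to be judged is not named.

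The consequence is confined to the supportive analysis. Its covariate set would be arbitrary, with shifts usually below 1 point and rarely above about 2.3. That could matter beside a borderline result, but the primary result adjusted for center and age group does not depend on it.

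The figures assume 144 per arm, the SD of 18 applied to change, independent covariates, correlations with change of 0 to 0.3, and, for the GEE runs, a within-patient correlation of 0.5 and dropout completely at random. The main-effect result for complete data is algebraic and needs none of the correlation assumptions.

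**What to change.** Drop the 10% rule. In its place, pre-specify one supportive adjusted analysis of the 24-month IKDC difference. It should include all seven listed baseline variables whatever their effect on the estimate, entered so that they can affect the follow-up scores, with sparse categories collapsed in advance. Report the difference with its 95% CI against the 8-point margin, beside the primary result. Correct the count from five to seven.

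In the text this takes about one sentence. The statistical cost is more than a few degrees of freedom: profession, ASA class, tear type and Kellgren-Lawrence grade are categorical, so the seven variables need roughly ten or more parameters. If they are fitted separately at each of the four IKDC follow-up visits, this becomes about 4 × 10 = 40. Restricting the adjustment to the 24-month difference and collapsing categories beforehand keeps this manageable for a supportive analysis with about 288 patients.

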In all models, missing data (intermittent/drop-out) will be analyzed on being missing completely at random (MCAR) or not (missing at random [MAR]). If not, each model will either be appropriately corrected or missings will be appropriately imputed (to be determined; e.g. last observation carries forward or multiple imputation). In the intention-to-treat analysis we already anticipate a 25% dropout which is non-ignorable (intervention related). Therefore, these data will be analyzed using a weighted GEE analysis. We will consult a statistician for all GEE analysis.

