#### Patient outcome analysis:

Effect measures in the economic evaluation are physical function, pain intensity and general health. Quality-adjusted life-years (QALYs) based on the Dutch tariff for the EuroQol will also be measured (22;29).

The analysis will be done according to the intention-to-treat principle. Missing cost and effect data will be imputed using multiple imputation according to the MICE algorithm developed by Van Buuren (30).

Full cost-effectiveness and cost-utility analyses will be performed. Incremental cost-effectiveness ratios (ICERs) will be calculated by dividing the difference in mean total costs between the treatment groups by the difference in mean effects.

Bias-corrected and accelerated bootstrapping with 5000 replications will be used to estimate 95% confidence intervals around cost differences and the uncertainty surrounding the ICERs. Rubin's rules will be used to pool the results from the different multiply imputed datasets. Uncertainty surrounding the ICERs will be graphically presented on cost-effectiveness planes.

Cost-effectiveness acceptability curves will also be estimated using the net benefit framework (31). Cost-effectiveness acceptability curves show the probability that APM is cost-effective compared with PT for a range of different ceiling ratios thereby showing decision uncertainty (32).

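### Correction for missing IKDC data depends on a low-power MCAR check, and it is unclear whether the unconditional weighted GEE covers the planned 10% loss to follow-up

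*Protocol*

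**What the plan says.** Section 10 of the protocol plans a GEE for the repeated IKDC scores and says that the method allows for "the fact that not all patients may be assessed at each time point (missing data"). It then sets a rule for every model: "missing data (intermittent/drop-out) will be analyzed on being missing completely at random (MCAR) or not (missing at random [MAR"]). The consequence follows: "If not, each model will either be appropriately corrected or missings will be appropriately imputed". The method is still to be determined, and last observation carried forward and multiple imputation are given as examples.

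The same paragraph makes one commitment that does not depend on the check: "In the intention-to-treat analysis we already anticipate a 25% dropout which is non-ignorable (intervention related"), and "Therefore, these data will be analyzed using a weighted GEE analysis".

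Section 6.4 lists two separate allowances: "We calculated that with 10% loss to follow-up after 24 months and 25% delayed APM in the PT group, 160 patients are needed per group". Section 7 (Delayed surgery group) keeps patients with delayed APM in the PT group for the intention-to-treat analysis. The note to Figure 1 in section 5 says that their follow-up for the primary outcome remains 24 months.

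For the economic evaluation, section 10 (Patient outcome analysis) says: "Missing cost and effect data will be imputed using multiple imputation according to the MICE algorithm". No MCAR condition is attached there.

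**The concern.** An unweighted GEE is generally valid only if data are missing completely at random. The rule leaves that analysis in place whenever the MCAR assessment raises no alarm. With few dropouts, the absence of an alarm says little, because a real difference between dropouts and completers can easily go unseen. If the assessment does raise an alarm, the remedy is chosen after the data have been seen, and one of the named options, last observation carried forward, is not valid under MAR in general.

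The trial is open and its primary outcome is a patient questionnaire, so patients doing badly on PT may stop responding. If that goes uncorrected, the 24-month PT mean is too high, and the error favours the non-inferiority claim that the trial is built to make.

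**Working it through.** **1. Are the 10% and the 25% separate?** Inputs from section 6.4: "Sample size is based on a power of 90%, an alpha of 0.05, a standard deviation of 18 points and a non-inferiority threshold of 8". The two allowances are 10% loss and 25% delayed APM. For a one-sided 2.5% test:

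n per arm = 2 × (1.960 + 1.282)² × 18² / 8² = 106.4, rounded up to 107.

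Applying both allowances gives 107 / (0.90 × 0.75) = 158.5, rounded up to 159, against the stated 160. Other combinations do not reproduce it: 107 / 0.65 = 165, and 107 × 1.1 × 1.25 = 148. The sample size therefore treats loss to follow-up and delayed APM as two different things.

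**2. Which patients does the weighted GEE cover?** The only 25% in the sample-size text is delayed APM, and the label of intervention-related dropout in section 10 fits those patients. Yet they stay under follow-up, so their IKDC scores should be observed. On this reading the unconditional weighting is attached to patients who are not missing, and the 10% who are missing fall under the conditional rule. Section 10 could also mean a true 25% dropout. The text does not settle it.

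**3. How much would a check miss at 10% loss?** Dropouts are 0.10 × 320 = 32 against 288 completers, or 16 against 144 within one arm. The protocol names no test for this check. I assume a two-sample comparison at two-sided 5%, the level that section 10 sets for all analyses. For a true difference of d SD:

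miss rate = 1 − Φ( d / √(1/n₁ + 1/n₂) − 1.96 )

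- Pooled, d = 0.5: √(1/32 + 1/288) = 0.1863; 0.5 / 0.1863 = 2.683; 1 − Φ(0.723) = 23.5%.
- One arm, d = 0.5: √(1/16 + 1/144) = 0.2635; 0.5 / 0.2635 = 1.897; 1 − Φ(−0.063) = 52.5%.

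A noncentral t calculation gives 23.7% and 53.0%. The size d is not in the protocol, so the range matters:

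| Assumed difference | 32 vs 288 | 16 vs 144 |
|---|---|---|
| 0.3 SD | 64% | 79% |
| 0.5 SD | 23.5% | 52.5% |
| 0.8 SD | 1% | 14% |

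If the dropout were 25%, the miss rate at 0.5 SD would be 3% pooled (80 vs 240) and 22% in one arm (40 vs 120).

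**4. What does a missed difference do to the estimate?** Take the SD of 18. If dropouts differ by 0.5 SD and make up 10% of an arm, the mean of the observed patients shifts by 0.10 × 0.5 × 18 = 0.9 points. The treatment contrast moves by about 0 if both arms shift alike, and by 0.9 if only one arm is affected.

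Now let PT dropout depend on interim IKDC, with a log-odds of 0.5 to 1.0 per SD and a correlation of 0.6 with the 24-month score (both assumptions), and let APM dropout be random. To first order the bias in a comparison of observed patients is log-odds × dropout share × correlation × SD:

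- 0.5 × 0.10 × 0.6 × 18 = 0.54 points
- 1.0 × 0.10 × 0.6 × 18 = 1.08 points

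Simulation of this case with 160 per arm and PT truly 8 points worse gave the same bias, 0.5 to 1.0 points towards non-inferiority. A pooled check passed in about 75% of trials at the weaker dependence and about 33% at the stronger. Among passing trials, false non-inferiority was roughly 4% to 8% across runs, against 2.5% nominal.

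**5. How far does this depend on the working correlation?** Step 4 corresponds to an independence structure. On the same data an exchangeable structure, with no other correction, brought false non-inferiority among passing trials at 10% loss to 2.2% to 2.9%, with bias of at most 0.2 points. When the true correlation was instead of autoregressive type (0.75), the exchangeable GEE gave 2.4% to 3.6%, with bias of about 0.2 to 0.3 points. The protocol states no working correlation.

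**The case against.** The strongest reply is that the conditional sentence is not the whole plan. The next two sentences assume non-ignorable dropout in advance and commit to weighting without waiting for any test. A reader might infer that missing data are corrected only if a check rejects MCAR; read together, the sentences do not say that. This part of the reply stands. What it does not answer is whether the weighting reaches the 10% lost to follow-up.

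A reader might also infer that the protocol takes a non-significant test as proof that the uncorrected GEE is safe. It does not say so. It names no test, variable or level for the assessment, and it promises that a statistician will be consulted on all GEE analyses. What remains is that the stated rule attaches no correction to the branch where MCAR is not doubted.

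It is tempting, too, to call the unconditional imputation in the economic evaluation a contradiction. It is not one. Different analyses may use different missing-data methods, and multiple imputation is also listed as an option for the effectiveness models. It shows only that a suitable method is already planned.

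Finally, the inflated false non-inferiority rates are a worst case. They depend mainly on the unstated working correlation, and a GEE that uses the within-patient correlation is close to nominal. That stands, and it limits the size of the problem.

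**Conclusion.** The point holds in a limited form. For missing IKDC data outside the anticipated 25%, the protocol makes correction conditional on an MCAR assessment that cannot carry that weight at 10% loss, and leaves the remedy open, last observation carried forward included. Whether the unconditional weighted GEE covers that 10% cannot be told from the text.

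The miss rates of 24% pooled and 53% within one arm rest on an assumed 0.5-SD difference, a two-sided 5% comparison and exactly 10% loss. The bias of about 0.5 to 1 point against an 8-point margin rests further on PT dropout driven by interim IKDC and an independence working correlation. It is modest, and most of it disappears under an exchangeable correlation. The change should be made, but the point does not show that the primary conclusion would be wrong.

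**What to change.** - Delete the MCAR condition and the last-observation-carried-forward option.
- State that the primary IKDC analysis always uses one MAR-valid method, whatever any MCAR assessment shows. Either multiple imputation by arm, with baseline and interim IKDC, age group and centre in the imputation model, or a weighted GEE or likelihood-based mixed model covering all missing IKDC scores would serve. Name one.
- State which patients the weighted GEE covers: those with delayed APM, those lost to follow-up, or both.
- Keep the comparison of dropouts with completers as description only.

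The cost is a change of wording and slightly more analysis work. Multiple imputation is already planned for the economic evaluation.
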